# IMPROVE*job* – Participatory intervention to improve job satisfaction of general practice teams: a model for structural and behavioural prevention in small and medium-sized enterprises – a study protocol of a cluster-randomised controlled trial

**DOI:** 10.1186/s13063-020-04427-7

**Published:** 2020-06-16

**Keywords:** Job satisfaction, Perceived psychological stress, Primary care, General practices, Participatory intervention, Psychological well-being, Effectiveness, Leadership, Structural prevention, Behavioural prevention

## Abstract

**Background:**

Perceived high chronic stress is twice as prevalent among German general practitioners (GPs) and non-physician medical staff compared to the general population. The reasons are multi-factorial and include patient, practice, healthcare system and societal factors, such as multi-morbidity, the diversity of populations and innovations in medical care. Also, practice-related factors, like stressful patient-staff interactions, poor process management of waiting times and lack of leadership, play a role. This publicly funded study evaluates the effectiveness of the newly developed participatory, interdisciplinary, and multimodal IMPROVE*job* intervention on improving job satisfaction among general practice personnel. The intervention aims at structural stress prevention with regard to working conditions and behavioural stress prevention for leaders and other practice personnel.

**Methods:**

In this cluster-randomised controlled trial, a total of 56 general practices will be assigned to either (1) participation in the IMPROVE*job* intervention or (2) the waiting-list control group. The IMPROVE*job* intervention consists of the following elements: three workshops, a toolbox with supplemental material and an implementation period with regular contact to so-called IMPROVE*job* facilitators. The first workshop, addressing leadership issues, is designed for physicians with leadership responsibilities only. The two subsequent workshops target all GP and non-physician personnel; they address issues of communication (with patients and within the team), self-care and team-care and practice organisation. During the 9-month implementation period, practices will be contacted by IMPROVE*job* facilitators to enhance motivation. Additionally, the practices will have access to the toolbox materials online. All participants will complete questionnaires at baseline and follow up. The primary outcome is the change in job satisfaction as measured by the respective scale of the validated German version of the Copenhagen Psychosocial Questionnaire (COPSOQ, version 2018). Secondary outcomes obtained by questionnaires and - qualitatively - by facilitators comprise psychosocial working conditions including leadership aspects, expectations and experiences of the workshops, team and individual efforts and organisational changes.

**Discussion:**

It is hypothesised that participation in the IMPROVE*job* intervention will improve job satisfaction and thus constitute a structural and behavioural prevention strategy for the promotion of psychological wellbeing of personnel in general practices and prospectively in other small and medium sized enterprises.

**Trial registration:**

German Clinical Trials Register: DRKS00012677. Registered on 16 October 2019. Retrospectively, https://www.drks.de/drks_web/navigate.do?navigationId=trial. HTML&TRIAL_ID = DRKS00012677.

## Contributions to the literature

This study will contribute as follows:
Few studies have evaluated participatory intervention strategies to improve job satisfaction in small and medium sized enterprisesThis study protocol describes a cluster randomised trial aiming to improve job satisfaction in general practice personnelThe intervention aims at activating the target groupThe study comprises behavioural and structural prevention strategiesIssues of leadership, communication and work organisation in practices are addressed.

## Background

Poor job satisfaction is an ongoing issue across many job domains worldwide [1, 2]. Due to the shortage of physicians in primary care in many countries, increased research efforts are directed to how to maintain and improve job satisfaction in this workforce [3–5]. Studies in various general practice populations in Europe and beyond showed that job satisfaction is profoundly influenced by work-related factors [5–7]. Factors that are known to decrease job satisfaction include too many working hours, administrative burdens, inadequate income, heavy workload, and lack of time and recognition [7]. Persistently low job satisfaction is related not only to chronic stress, burnout, depression, early retirement and other indicators of physicians’ health, but is also linked to less satisfactory patient outcomes [8–15]. A study by Viehmann et al. showed that physicians and non-physician personnel in general practices are twice as likely to experience high chronic stress compared to the general population [10]. In the same population, physicians in group practices had a higher rate of burnout than those from single practices, with young, part-time, female physicians employed there having the highest burnout rate, even when compared to group practice owners [16]. Various reasons for high strain were identified; key factors were quality of leadership, difficult patient-encounters and practice organisation [10, 17, 18].

Various approaches to improving the mental wellbeing of healthcare workers have been evaluated [19, 20]. Many approaches address individual behaviour such as stress management, meditation, or training in self-care [21, 22]. However, based on the European principles of occupational health and safety, interventions should first target the work environment of individuals and address behavioural prevention thereafter [23]. A review by Montano et al. about the effectiveness of organisation-related interventions showed that health-promoting effects were achieved among employees when interventions simultaneously focused on work equipment, work processes and working conditions [24].

Having identified lack of leadership, difficult patient-encounters and practice organisation as problems in German general practices [10, 18], the IMPROVE*job* intervention was developed under the leadership of a family medicine physician and scientist, following an interdisciplinary and participatory approach: experts from the fields of general practice and family medicine, occupational and psychosomatic medicine, operations research, health promotion and epidemiology provided input into the various areas; a research support group with GPs and practice assistants was repeatedly asked for input and feedback to ensure that the intervention is tailored to the needs and capacities of general practice teams. The intervention focuses on reducing work-related psychological stress, to increase job satisfaction. It consists of three workshops (i.e. a leadership workshop for physicians with leadership responsibilities and two workshops for the entire practice team), a toolbox and so-called IMPROVE*job* facilitators to support implementation. Learning contents for participants focus on issues relating to leadership, communication and work processes. The main aim of this cluster-randomised controlled trial (cRCT) is to investigate whether the IMPROVE*job* intervention increases job satisfaction amongst general practice personnel.

## Methods/design

### Study design

This cRCT evaluates the effectiveness of the IMPROVE*job* intervention in improving job satisfaction (primary outcome) among practice personnel. Randomisation will take place at practice level, i.e. all personnel in the practice will be assigned either to the intervention or to the control group. The study will be conducted according to the waiting-list control principle, i.e. practices of the intervention group will receive the IMPROVE*job* intervention after the baseline data collection; the control group will receive the workshops after completion of the study. For details see Fig. 1.

**Fig. 1 Fig1:**
[figure not shown]
Study design: cluster-randomised controlled trial with intervention practices and waiting-list control practices

### Participants and recruitment

The study will be conducted in general practices of the North Rhine region in Germany. Urban and rural medical practices are selected to ensure better generalisation of the results. Practices will be drawn as random samples from an official list of registered general practice physicians of the Association of Statutory Health Insurance Physicians of North Rhine (in German, *Kassenärztliche Vereinigung Nordrhein*) in these selected areas and from a list of teaching practices of regional universities. We previously showed that teaching practices are typically easier to recruit and do not differ from non-teaching practices with regard to health service characteristics [25]. We therefore aimed for an approximately equal distribution of teaching and non-teaching practices in the final sample.

The practices will be contacted by the Institute of General Practice and Family Medicine of the University of Bonn. Depending on available contact details, practices will be sent invitation letters by mail, fax and/or email, each of which include participant information and an informed consent form for the practice owner. Practices will then be contacted by phone to provide additional study information. As soon as the practice owner has given written consent, a visit by a study nurse from the Center for Clinical Trials in Essen (in German, *ZKSE, Zentrum für klinische Studien Essen*), is scheduled. During this visit, the study nurse will obtain informed consent from each participating team member, distribute and collect the baseline questionnaire data, and complete an observational occupational health and safety form. In the consent form, participants are informed that they are free to discontinue study participation at any time. Questionnaires will be checked for completeness of data. To promote participant retention and to prevent loss to follow up, each participant will receive 50€ after the intervention. In addition, IMPROVE*job* facilitators will motivate participants to complete the study.

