#### IMPROVE*job* facilitators

The facilitators are trained members of the research team who will accompany the practices during the change processes by on-site meetings in the practice and/or by phone. Prior to the workshops, the facilitators will be trained in change processes, the setting of GP practices and qualitative data collection in two training sessions. The facilitators concentrate on processes and developments within the practices, but they do not engage in active coaching. They are conceptualised as process companions who remind the practice teams of the project and support the implementation of the intervention. In addition, the facilitators will collect qualitative data in the practices to analyse the relevance, feasibility and implementation of the intervention. The facilitators will take part in the intervention workshops where they will meet the study participants. Also, they will note the practice goals set by each participating practice. After the workshops the facilitators will offer practices to contact them regularly, e.g. once a month, to facilitate the implementation.

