### Control group

This study will use a waiting-list control approach. After completion of the follow-up data collection, practices in the control group will be offered the same IMPROVE*job* workshops as practices in the intervention group, including access to the toolbox. The project duration and funding does not allow for IMPROVE*job* facilitators to be involved in the waiting list control group.

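### A stated retention measure, facilitator encouragement to complete the study, operates only in intervention practices, while the confirmatory analysis takes only participants with both questionnaires

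*Protocol article*

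**What the plan says.** The section Participants and recruitment of the protocol article names two measures against loss to follow-up. One is cash: "each participant will receive 50€ after the intervention". The other is personal encouragement: "facilitators will motivate participants to complete the study". Neither sentence names an arm.

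Other sections show where the facilitators work. Under IMPROVEjob facilitators: "The facilitators will take part in the intervention workshops where they will meet the study participants". The same section continues: "After the workshops the facilitators will offer practices to contact them regularly, e.g. once a month". The abstract places this contact in the 9-month implementation period, when "practices will be contacted by IMPROVE*job* facilitators to enhance motivation". The Control group section then states: "The project duration and funding does not allow for IMPROVE*job* facilitators to be involved in the waiting list control group".

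On timing for controls, that section says: "After completion of the follow-up data collection, practices in the control group will be offered the same" workshops as the intervention group.

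The section Data management, statistical analyses and steering committee defines the confirmatory analysis. It is labelled intention-to-treat but includes those who completed the job satisfaction scale at both baseline and follow-up. The same section says that missing data will be handled by imputation, without saying in which analysis. The Randomisation section says that practice personnel cannot be blinded.

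**The concern.** The first section reads as if facilitators supported retention for everyone in the trial. The Control group section shows that they cannot. One of the two named retention measures therefore acts in one arm only, on participants who know their allocation and may leave at any time.

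This matters because of how the primary analysis set is defined. If only people with both questionnaires count, any effect of arm on who returns the second questionnaire enters the primary comparison directly. Randomisation balances those who start, not those who remain.

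The cash measure has a smaller defect. Its payment point is set relative to the intervention. Controls are offered the workshops only after follow-up is complete, so the wording does not say when they are paid. Read literally, their payment would come after the follow-up questionnaire and would not be linked to returning it.

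**Working it through.** **Step 1: the passages side by side.**

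| Element | Intervention arm | Control arm |
|---|---|---|
| Facilitator encouragement to complete the study | Yes: met at the workshops, then contact offered regularly | Ruled out by the Control group section |
| 50€ | Each participant, after the intervention | Each participant, but the payment point is undefined |
| Other follow-up contact | Not described | Not described |
| Confirmatory analysis set | Both questionnaires completed | Both questionnaires completed |

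Only the first row is a stated difference between the arms. The second is an ambiguity. The third is silence in a condensed article.

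**Step 2: the plan's own power figures.** Inputs from Sample size calculation: SD 15, ICC 0.05, k = 26 practices per arm, difference 7.3, two-sided α = 0.05. With m participants per practice, the design effect is 1 + (m − 1) × 0.05 and SE = 15 × √(2 × design effect / (k × m)). Power comes from the noncentral t distribution with 2(k − 1) = 50 degrees of freedom.

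- m = 3: design effect 1.10, SE = 15 × √(2.20/78) = 2.52, power 81.1% (stated: 81%).
- m = 4: design effect 1.15, SE = 15 × √(2.30/104) = 2.23, power 89.4% (stated: 89%).

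The stated figures reproduce and are not in dispute.

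**Step 3: bias from differential loss.** The documents give no individual loss rates and no difference in outcome between leavers and stayers. Everything in this step is an assumption.

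Let L be the fraction lost in an arm and g the mean change in stayers minus that in leavers. The mean over everyone randomised in the arm is (1 − L) × stayers + L × leavers = stayers − L × g. The completer mean is therefore off by L × g. With the same g in both arms:

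bias in (intervention − control) = (L intervention − L control) × g

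Sizes, ignoring sign:

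| Difference in loss | g = 0.25 SD (3.75 points) | g = 0.5 SD (7.5 points) | g = 0.67 SD (10 points) |
|---|---|---|---|
| 0 | 0 | 0 | 0 |
| 10 percentage points | 0.38 (5% of 7.3) | 0.75 (10%) | 1.0 (14%) |
| 20 percentage points | 0.75 (10%) | 1.5 (21%) | 2.0 (27%) |

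Against the minimally important difference that the plan cites, 0.4 × 15 = 6 points, the first non-zero row is 6 to 17%.

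The sign depends on who leaves and from which arm. If more controls are lost and leavers have the worse change, the completer mean in controls is too high and the effect is understated. If leavers have the better change, or more of the intervention arm is lost, the sign reverses. If g differs between arms, even equal loss can bias the comparison.

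**Step 4: power.** Same method, letting m differ between arms:

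- 3 per practice, 20% lost in both arms (2.4 and 2.4): 73%.
- 3 per practice, 20% lost in controls only (3 and 2.4): 77%.
- 4 per practice, 20% lost in both arms (3.2 and 3.2): 83%.

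These losses in power come mainly from the number of people lost, not from its imbalance. Three per practice is also a low base. The workshop section expects 5–6 practices to bring 8–10 physicians and 15–25 assistants, that is between 23/6 = 3.8 and 35/5 = 7 people per practice.

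**The case against.** Several points on the other side are sound.

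- **The 50€.** A reader might infer that controls are paid differently or not at all. The text does not support that. It says each participant, names no arm, and gives retention as the purpose. Only the payment point for controls is unclear, and payment at study end for everyone may already be intended.
- **Contact with controls.** A reader might infer that control practices hear nothing for nine months. The article excludes facilitators from that arm, not contact by the study centre. It describes follow-up logistics for neither arm, and such detail is commonly left to a full protocol.
- **Certainty of differential loss.** A reader might infer that completion will differ by arm, with more controls lost. That is not established. Controls have later workshops to wait for, and intervention staff carry the burden of workshops and implementation, so the difference could be nil or run the other way.
- **Imputation.** The plan mentions it, so calling the trial purely a completers' analysis would ignore a sentence. But that sentence is tied to no analysis, while the confirmatory set is defined explicitly as those with both measurements. Imputation would in any case help only as far as the observed data explain who leaves.
- **Inherent asymmetry.** Comparing a facilitated intervention with a waiting list always means unequal contact. That is true, and it limits what any fix can achieve. It does not explain why encouragement to complete the study, which is a trial procedure, should be given to the people who deliver the intervention.

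What remains is that a named retention measure exists in one arm only and the primary analysis set is exposed to it.

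**Conclusion.** The point holds as an avoidable risk, not as a demonstrated bias. Facilitator encouragement to complete the study is a stated retention measure confined to the intervention arm, the payment point of the 50€ is undefined for controls, and the confirmatory analysis set depends on completing follow-up.

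Size and direction cannot be known from the document. If loss differs by 10 percentage points and the stayer–leaver gap is 0.25 to 0.67 SD and equal in both arms, the bias is about 0.4 to 1.0 points, or 5 to 14% of the 7.3-point target. It is zero if loss and gap are both equal across arms.

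A reader might also infer that uneven loss would leave the trial underpowered. The figures do not support that as the main concern: 73% arises from 20% loss in both arms at the planning minimum of three per practice, and with four per practice the same loss leaves 83%. The issue is bias. It is worth correcting because the remedy is cheap.

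**What to change.** 1. Have the study centre send the same scheduled follow-up reminders, with the same number and wording, to every participant in both arms, so that retention does not rest on facilitators. Facilitators keep their implementation role.
2. State that the 50€ is paid on return of the follow-up questionnaire in both arms.
3. Report follow-up completion by arm and by role (physicians with leadership responsibility, other physicians, practice assistants).

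The cost is a few extra mailings or calls by existing staff and a clarified payment date. The downside is slightly more study contact for controls. According to Trial status, recruitment ended on 4 March 2020, so with follow-up after 9 months the change could still reach the later-recruited practices when the article appeared in June 2020. Facilitator contact remains part of the intervention and will still remind intervention teams of the project, so the asymmetry is reduced, not removed.

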### Inclusion and exclusion criteria

Practices will be included if at least one practice physician is registered as a GP with the Association of Statutory Health Insurance Physicians of North Rhine with or without teaching obligations. Practice teams are eligible for participation if at least one physician with leadership responsibilities and at least one practice assistant provide informed consent for study participation. Physicians with leadership responsibilities include physician practice owners and employed practice physicians with respective duties. Our aim is to recruit all members of a practice team including employed physicians and practice assistants in training.

Exclusion criteria are a foreseeable special situation that might interfere with the completion of the study, such as practice relocation or retirement of the practice owner; practices that are not primarily involved in primary care (e.g. predominantly providing psychotherapy or pain therapy); and practices that participated in the development of the IMPROVE*job* intervention or in the feasibility study of the intervention.

### Randomisation

General practices will be randomised by means of several random lists. These lists include single and group practices and teaching and non-teaching practices, to achieve a roughly equal distribution in both the intervention and the control groups. We chose the stratification factor of (a) single/group practice, because structural characteristic, leadership responsibilities and indicators of psychological wellbeing may differ between practice types [10, 16] and (b) teaching/non-teaching practice, as this factor may influence the motivation to participate in the intervention (and may indirectly influence its effects). The randomisation list is generated by an employee of the ZKSE who is not involved in the selection of the practices. Practices will be randomised after baseline data collection, to ensure that study nurses are blinded for the first site visit. The randomisation allocation will be transferred to scientists at the Institute of General Practice and Family Medicine in written form, who will inform the practices by phone and letter. Blinding of the scientists and the practice personnel is not possible due to the participatory concept of the intervention, which includes workshops. Data analysts will follow a predefined protocol for analysis to avoid bias.

### Questionnaires and outcome measures

The primary outcome of this study is an improvement in job satisfaction. To measure job satisfaction, the respective scale of the German version of the Copenhagen Psychosocial Questionnaire based on the international COPSOQ III version (German COPSOQ, version 2018) will be used (www.COPSOQ.de). The COPSOQ is a validated questionnaire that measures psychosocial factors at work [26–28]. The job satisfaction scale of this instrument consists of 6 items (B11: 1–5) and is combined with an additional global item (B11: 7 “how pleased are you with your job as a whole, everything taken into consideration?”). The outcome “ob satisfaction” was selected as the primary outcome, because the IMPROVE*job* study evaluates a complex intervention, which addresses various factors known to influence the psychological wellbeing of practice personnel.

The following additional COPSOQ scales will be used as secondary outcomes: quantitative demands (B1: 1, 3, 5), emotional demands (B1: 6–7), work pace (B1: 2, 4), work-privacy conflict (B2: 1–2), and additional items (B2: 3–4, B2: 5) “delimitation” (B2: 6–7), predictability (B6: 1–2), role clarity (B6: 3–5), role conflicts (B6: 6–8); social support (B8: 1–4), feedback (B8: 5–6), social relations (B8: 7), sense of community (B8: 8–9) and bullying (B8: 10). To calculate scale scores for each dimension, the COPSOQ will be transformed as recommended [29]. Scales will be transformed into scores ranging from 0 (minimum value, “do not agree at all”) to 100 points (maximum value, “fully agree”).

The following additional aspects will be addressed using questionnaires: (1) leadership, (2) general health (3) work behaviour, (4) chronic stress, (5) occupational health and safety culture, (6) stress coping strategies applied by participants, (7) work organisational issues including waiting times, team roles and team activities and (8) team activities and roles.

